## Abstract

**Background:**

Raising children in new social and cultural contexts can be challenging for parents. In order to help parents address these challenges, the Norwegian government has instituted a policy of mandatory parent training for families who settle in Norway as refugees. The Incredible Years (IY) and The International Child Development Programme (ICDP) have been widely adopted throughout Norway. They have similar aims: to improve parenting through positive parenting practices and development of attachment behaviors. We will evaluate the use of these programs and a measurement feedback system (MFS) to give regular feedback to interventionists about parents’ progress during the course of the parenting intervention.

**Methods:**

The study is a mixed method, randomized factorial design aimed at evaluating the effect of parenting interventions and the use of feedback to address parental stress, child behavior, resilience, and parents’ mental health. Factor 1 is based on random assignment to one of the parenting interventions IY or ICDP. The parenting interventions are delivered over 15 weeks (IY) or 12 weeks (ICDP) in group-based settings. Factor 2 is based on random assignment of the parenting groups to the (a) with MFS or (b) without MFS condition. The MFS is answered weekly via a phone app, MittEcho, and results are sent to group leaders in the MFS condition. Additionally, the study explores the experiences of families settling in a new cultural context and participating with parenting programs via qualitative interviews. Participants will be recruited from a population of parents with children between the age of 6 and 12 years who settled in Norway as refugees within the previous 9 years. The target sample size is *N* = 360; *n* (IY) = 180, *n* (ICDP) = 180 families. This study is a collaboration between first-line, municipal services; their national governing agencies; family representatives; and a national network of research organizations.

**Discussion:**

This study endeavors to provide information about what helps families with refugee background integrate successfully into new cultural contexts with different laws, norms, and expectations. Whether or not these interventions can help to normalize this experience, reduce stress, and provide parents with new tools to improve their parenting and the lives of their children are important questions which we address. These findings can lead to the further establishment of evidence-based practices in Norway.

**Trial registration:**

ISRCTN35008070. Registered on February 24, 2020

## Administrative information

Note: the numbers in curly brackets in this protocol refer to SPIRIT checklist item numbers. The order of the items has been modified to group similar items (see http://www.equator-network.org/reporting-guidelines/spirit-2013-statement-defining-standard-protocol-items-for-clinical-trials/).

## Introduction

### Background and rationale {6a}

Raising children in new countries is challenging for most parents [1, 2]. Parents with refugee background have additional pressures to the usual stress that parents face [3]. These challenges could be related to war exposure [4], acculturation [5], poor mental health, and reduced family functioning [6]. These factors affect parenting differently [4], but they are seen as risk factors for child maladjustment [6]. Positive parenting coping strategies are demonstrated as protective factors to these child maladjustment risks [7, 8]. Parenting interventions such as the Incredible Years (IY) and the International Child Development Program (ICDP) may be uniquely positioned to address this challenge. The Incredible Years has been successfully adopted in many cultures and contexts [9]. Furthermore, IY has shown positive results in randomized trials with selected populations [10], though never with refugee populations. ICDP is a universal parent training program used in over 30 countries worldwide since the 1990s. The International Child Development Program (ICDP) has evidence of effect from other countries [11–15], but not from this particular population in Norway [16]. Both of these programs are widely implemented in social welfare and refugee services throughout Norway. Both of these interventions involve a group-based environment to learn proactive parenting skills to improve the family climate and give parents positive skills to help guide their children. The present study will provide knowledge regarding the effectiveness of these parenting interventions for families with refugee background who are integrating into Norwegian culture.

There has also been a growing need for improving treatment quality using measurement feedback systems (MFS) during treatment in mental health services [17]. It is believed that MFS can improve treatment quality by offering regular feedback to interventionists concerning the well-being of their clients. There are no MFS known to the project team that expressly addresses the needs of professionals working with group-based parenting interventions. To address this need, the project team developed an app that participants can access from their phone to answer a series of questions about their experience with the parenting interventions. The app, MittEcho, was developed to address this population and these interventions.

This study will have a mixed method, randomized factorial design that will include surveys, video observations, and interviews. Mixed methods refers to the use of qualitative and quantitative data collected together to address the primary research questions. The qualitative interviews will be conducted to gather information about the experiences of parents, children, and interventionists with relation to the overall questions of the utility and effectiveness of the interventions. The quantitative surveys will allow for the statistical testing of the primary and secondary outcomes. The multi-factorial design is a means to evaluate the parenting interventions (factor 1) and assess whether the addition of the MFS (factor 2) improves overall outcomes.

This study employs a multi-informant approach with data obtained from parents, children, teachers, and program group leaders. User perspectives and satisfaction will be explored throughout the project-period and used to adjust and adapt study procedures. Although IY and ICDP are implemented throughout Norway, the effectiveness of the programs for refugee families has not been established. This study, therefore, builds upon existing infrastructure to support these interventions and provides new, useful information for policymakers regarding the effectiveness of these programs. This can lead to the establishment of evidence-based practices in Norway.

### Objectives {7}

The primary aims of the present study are to evaluate the effectiveness of the IY and ICDP parenting interventions for improving primary outcome measures of parenting skills, lowering parental stress, and reducing problem behavior in children. The parenting programs are expected to have similar outcomes. Furthermore, the present study is an evaluation of the effectiveness of systematic, measurement feedback to improve treatment outcomes for refugee parents; therefore, we expect better outcomes for families whose group leaders are receiving systematic feedback about their group’s progress. This is a mixed method inquiry to evaluate whether IY and ICDP are appropriate interventions to address the challenges refugee parents experience while raising children in a new cultural context. We will conduct surveys and interviews of parents attending IY and ICDP groups and interviews with some of their children. The IY and ICDP group leaders will also be invited to fill out surveys and interviews. This multi-informant, multi-method approach provides different perspectives on the effectiveness of the interventions and the experiences of parents and practitioners. The interviews will contribute to better, overall knowledge of the usefulness of IY and ICDP for refugee parents with focus on who benefits the most from the interventions. Additionally, we will evaluate videos of IY sessions for analysis of the group dynamics, how families interact, and how they experience a group-based parenting intervention. IY collects video recordings as part of standard procedure, these recordings are not available for ICDP.

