### Trial design {8}

The study has a two-by-two factorial, mixed methods design (see Table 1). The sample will consist of families with refugee background who have settled in Norway within the previous 9 years. Survey data will be collected pre-intervention (T1), mid-way through the intervention (T2), after the intervention (T3), and 1 year following intervention completion (T4). Qualitative data collection will begin after the families have completed the intervention.

**Table 1 Tab1:** Study conditions

		A. Parenting program	B. Measurement feedback
	Condition 1	IY	MittEcho
	Condition 2	IY	None
	Condition 3	ICDP	MittEcho
	Condition 4	ICDP	None

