#### Factor A: parenting program

Families will be randomized into either IY or ICDP parenting program at the beginning of each semester. Each parenting program is described in the “Intervention description {11a}” section.

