### Implementation {16c}

To preserve the factorial design, we need to randomize to four conditions (see table in the “Trial Design” section of this document). We cannot randomize families to four separate conditions at each site, because this would require running four groups at each site every semester (see also the “Sequence generation {16a}” section). It would not be feasible for the municipalities to conduct four groups in parallel due to the staffing requirements. Therefore, randomization in PIRM has two stages: stage 1, randomization to MFS condition at the group level, and stage 2, randomization of families to IY or ICDP parenting groups.

Recruitment of families at each site will be ongoing. Families will be randomized when (a) a maximum of 12 families are recruited or (b) a cutoff date is reached each semester. The cutoff date will be established by the amount of time it takes to complete a group, (i.e., 15 weeks for IY, 12 weeks for ICDP). In Norway, summer holidays usually occur between June and August; therefore, groups must have adequate time to finish within the time period from January to June or late August to December.

The parenting groups (2 per site) are randomly assigned to one of the MFS (Y/N) conditions so that one group at each site will be in the MFS conditions. For example, at site 1, the ICDP group is randomly assigned to the MFS condition during the first semester. The following semester the groups will be reassigned and the IY group at site 1 may end up in the MFS condition.

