## Discussion

The PIRM study takes place within the context of recent requirements for refugee families to participate in parenting programs. The knowledge gained regarding effects of the parenting interventions will further inform policymakers regarding the use of these programs for families with refugee background. Our results will further provide guidance about the use of a weekly measurement and feedback within the context of these interventions. This guidance will evaluate the effectiveness of MFS with parenting interventions, as well as its feasibility of implementation in first-line preventive services.

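### The primary aim is stated as the effectiveness of IY and ICDP, but every randomised condition receives one of them, so the trial can estimate only IY versus ICDP and the added effect of MFS

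*Protocol article*

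**What the plan says.** **Aim.** Objectives {7}: "The primary aims of the present study are to evaluate the effectiveness of the IY and ICDP parenting interventions", judged on parenting skills, parental stress and child problem behaviour. The same section adds: "The parenting programs are expected to have similar outcomes".

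**Framing.** Background and rationale {6a} says that the programmes' effectiveness in refugee families has not been established and that the study "provides new, useful information for policymakers regarding the effectiveness of these programs". It also gives the factorial design the task of evaluating the programmes: "The multi-factorial design is a means to evaluate the parenting interventions (factor 1) and assess whether the addition of the MFS (factor 2) improves overall" (quote cut one word short).

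**Design.** Trial design {8}: "The study has a two-by-two factorial, mixed methods design". The four conditions in Table 1 are IY with MittEcho, IY alone, ICDP with MittEcho, and ICDP alone. Factor A: "Families will be randomized into either IY or ICDP parenting program at the beginning of each semester". Implementation {16c} describes the randomisation as "stage 1, randomization to MFS condition at the group level, and stage 2, randomization of families to IY or ICDP parenting groups".

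**Comparisons.** The quantitative part of Outcomes {12} compares change between the levels of the two factors. Sample size {14} powers IY (180) against ICDP (180) and MFS (180) against no MFS (180). Statistical methods {20a} models change in the intervention groups adjusted for baseline, and looks at the interaction if power allows.

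**The concern.** The aim asks whether each programme works in this population. That is a comparison with what would have happened to the same families without a programme. No condition supplies that comparison, so the stated primary aim goes beyond what the randomisation can show.

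What is at stake is what the trial may conclude. The protocol addresses policymakers and hopes to support evidence-based practice. If the aim stays as worded, an improvement over time in both arms could be taken as proof of effectiveness and credited with the authority of a randomised trial, although that part of the evidence would be an uncontrolled before-after change.

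**Working it through.** **1. Which contrasts the sample size belongs to.** Inputs from Sample size {14}: significance level 0.05, power 0.80, d = 0.30 (so SD = 1). Sidedness is not stated; two-sided is assumed. Families are treated as independent, because the step serves only to identify the contrast.

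- Needed per level: n = 2 × (1.960 + 0.842)² / 0.30² = 174.4, so 175 per level and 350 in total. The plan's 360 is 10/350, or about 3%, above this.
- Power at 180 per level: SE = √(2/180) = 0.1054; 0.30/0.1054 − 1.960 = 0.886; power = 0.81.
- Smallest d detectable with 80% power: 2.802 × 0.1054 = 0.295.
- A one-sided test would need 138 per level, 276 in total, which does not match 360.

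So N = 360 is reproduced as 180 against 180 for either main effect.

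**2. What is available for programme versus no programme.** The plan has 4 conditions × 90 families = 360. All four contain IY or ICDP, so 0 of 360 families are randomised to no programme. No power can be calculated for that comparison.

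**3. What each contrast estimates.** Let m₀ be the mean outcome without a programme, and let e(IY) and e(ICDP) be the programme effects.

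- Factor 1: [m₀ + e(IY)] − [m₀ + e(ICDP)] = e(IY) − e(ICDP). The untreated mean m₀ cancels.
- Factor 2: MFS minus no MFS, with a programme on both sides. Again m₀ cancels.
- The programme-by-MFS interaction is a difference between such differences, and m₀ cancels there too. Sample size {14} also leaves it unpowered.

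None of these recovers e(IY) or e(ICDP) alone.

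**4. Adding the protocol's own expectation.** If outcomes are similar, e(IY) ≈ e(ICDP) = e and the factor 1 contrast is near 0 for any e. Take e = 0 in both arms, then e = 0.30 in both arms: the contrast is 0 each time, and a two-sided 5% test rejects 5% of the time each time. Both programmes working and neither working cannot be told apart.

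**5. What is left.** Change within an arm from T1 to T3 equals e plus the change that would have occurred anyway. The second part is unknown. It includes further time in Norway, child maturation, and other parenting or mental health care, which section {11d} leaves unrestricted. The interviews can speak to usefulness and experience, but they do not estimate a causal effect.

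**The case against.** **Mandatory training.** The section on choice of comparators {6b} says that parent training is a mandatory part of the introduction programme for refugees and that both programmes are among those named for that use. An untreated arm may therefore have been unrealistic, and a head-to-head comparison is a sensible policy question. This stands as a likely explanation of the design, though the section does not give it as the reason. It does not make effectiveness estimable.

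**Effectiveness could mean comparative effectiveness.** This reading fits the Discussion, "The knowledge gained regarding effects of the parenting interventions will further inform policymakers regarding the use of these programs", which can be read as a choice between mandated options, so that sentence is weak support for the point. It does not fit the Background, where the gap is whether the programmes work in this population, not which works better.

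**No before-after test is planned.** A reader might infer that the protocol intends to test within-arm change and report it as proof of effectiveness. It does not say so: the comparisons in {12}, {14} and {20a} are between factor levels. The point is only that the aim as worded has no other quantitative source.

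**Size of the drift.** A reader might also want to set expected regression to the mean against the planned d = 0.30. The documents do not support this. Eligibility {10} sets no symptom threshold, so there is no evidence of selection on poor scores. Moreover, d = 0.30 is a difference between randomised levels, in which drift common to both cancels.

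**Left to an analysis plan.** The aim and the conditions are both fixed in the protocol. No analysis plan can create a programme versus no-programme contrast from these arms.

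**Conclusion.** The point holds as a mismatch between aim and design. The planned contrasts are valid and the sample size reproduces for them, but none of them answers whether IY or ICDP is effective in refugee families. With similar outcomes expected, factor 1 is uninformative on that question.

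The size is structural: 0 of 360 families without a programme. No bias figure is given, because the documents offer nothing from which to derive one. The conclusion rests on Table 1 and the two randomisation stages as written, with no external or untreated comparison described. It does not mean that the trial is invalid or that an untreated arm should have been included. The wording should be corrected because it governs what the trial may claim.

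**What to change.** - In Objectives {7}, restate the primary aim as the comparative effect of IY versus ICDP and the added effect of MFS on the primary outcomes.
- Bring the matching sentences in Background and rationale {6a} into line, including the one on what the factorial design evaluates.
- State that any change from T1 within an arm is descriptive and uncontrolled, and will not be reported as evidence that either programme is effective.
- Optionally, note in section {6b} whether the mandatory training policy is why there is no condition without a programme.

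The cost is a narrower claim. Randomisation, sample size, outcomes and model are unchanged, and no new arm or data is needed.

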### Trial design {8}

The study has a two-by-two factorial, mixed methods design (see Table 1). The sample will consist of families with refugee background who have settled in Norway within the previous 9 years. Survey data will be collected pre-intervention (T1), mid-way through the intervention (T2), after the intervention (T3), and 1 year following intervention completion (T4). Qualitative data collection will begin after the families have completed the intervention.

**Table 1 Tab1:** Study conditions

		A. Parenting program	B. Measurement feedback
	Condition 1	IY	MittEcho
	Condition 2	IY	None
	Condition 3	ICDP	MittEcho
	Condition 4	ICDP	None

#### Factor A: parenting program

Families will be randomized into either IY or ICDP parenting program at the beginning of each semester. Each parenting program is described in the “Intervention description {11a}” section.

#### Factor B: MFS

Group leaders who are using the MFS system (condition 1 and condition 3) will get weekly feedback based on the answers from parents in the MittEcho app. The feedback will be displayed graphically in a web-based login portal. Further description of MittEcho is found in the “Intervention description {11a}”section.

## Methods: participants, interventions, and outcomes

### Study setting {9}

Data for the present study will be collected from municipal agencies (e.g., refugee services, social welfare services) who work directly with parents in the target population. Sites will be recruited to join the study from all regions in Norway: Eastern, Southern, Western, Central, and Northern. The current list of participating study sites can be accessed on the project website: https://uit.no/research/pirm.

### Eligibility criteria {10}

Study participants will be recruited from several populations. The primary participants in the study are parents with a refugee background who have settled in a Norwegian municipality within the previous 9 years. They must also have at least one child between 6 and 12 years old. In order to participate in the study, the parents must be able to understand one of the eight study languages, which was chosen based on input from integration services in Norway: Norwegian, English, Arabic, French, Swahili, Turkish, Tigrinya, or Somali. Interview subjects are chosen with the desire for balance when it comes to interventions, age, gender, and background.

### Who will take informed consent? {26a}

Participants will be invited to join the study by local child welfare, municipal health stations, and municipal services for refugees. These services will identify potential participants based on inclusion criteria. Information will be given directly to parents by the services on behalf of the project with an invitation to participate in the study. Persons who are interested in participating will then return the signed consent to the project via electronic registration or postal service. All written and oral information is given in the families’ preferred available language. If necessary, a certified interpreter is used. The services will not give personally identifying information about potential participants to the project; however, we will get some information regarding the numbers of families invited so that we can estimate our response and recruitment rates.

Parents/guardians will give consent on behalf of their children. The children themselves will be given understandable information about the intent of the project and their participation in the interview. At the beginning of the interview, verbal assent from the children will be obtained. It will be emphasized that their participation is voluntary and that they can withdraw from the project at any point, even though their parents have given consent.

Parents and children in refugee families are considered a vulnerable group and the project is aware that there is a heightened responsibility to consider the well-being of vulnerable individuals that take part in research. Extra care will be taken in order to limit any detrimental effects on these individuals. The project will communicate that participation is voluntary and that there will be no negative consequences for participants who wish to withdraw from the project (or parts of the project), including that it will not affect their relationship with any services they are in contact with, or help received from different agencies (e.g., the services for refugees, health stations etc.).

